### Implementation and study procedures

In this study, intravenous drip of salvianolate will be performed during coronary angiography and the subsequent 7 days and its effects on microcirculatory disturbance will be assessed via the IMR change and total ischemic burden. The study protocol is shown in Fig. 1 and Table 2, which is divided into three phases, including screening, immediate phase, and in-hospital follow-up.

**Fig. 1 Fig1:**
[figure not shown]
Flow chart. FFR, fractional flow reserve; IMR, index of microcirculatory resistance; cTnT/cTnI, cardiac troponin T/I

**Table 2 Tab2:** The study plan

	Screening	Immediate phase (intravenous drip of salvianolate for 30 min)	In-hospital follow-up
	Day 1	Day 1	Day 7
Inclusion/exclusion criteria	X		
Informed consent	X		
Randomization	X		
Demographic information	X		
Medical history	X		
Vital signs	X	X	X
Physical examination	X		X
Concomitant medications	X		X
CBC	X		X
Scr, BUN, UA	X		X
K, Na, Cl	X		X
ALT, AST, BIL	X		X
Fasting glucose/lipids	X		X
cTnT/cTnI	X		X
Electrocardiography	X		X
Echocardiography	X		X
**Medication**			
Salvianolate injection		X	X
**End points**			
Seattle angina scale	X		X
Quality of life scale	X		X
Holter electrocardiography	X		X
6-min walk test	X		X
IMR	X	X	

*CBC*, complete blood count; *Scr*, serum creatinine; *BUN*, blood urea nitrogen; *UA*, uric acid; *K*, potassium; *Na*, sodium; *Cl*, chloride; *ALT*, alanine aminotransferase; *AST*, aspartate aminotransferase; *BIL*, bilirubin; *cTnT/cTnI*, cardiac troponin T/I; *IMR*, index of microcirculatory resistance

In the screening stage, the investigator conducts a baseline assessment and gets the informed consent and randomization. Coronary angiography, FFR, and IMR will be used to determine whether the inclusion and exclusion criteria are met, and then informed consent should be signed by the patient or the authorized person. The web-based randomization assigned those eligible patients 1:1 ratio to either the salvianolate or the placebo group. The secretary of the catheterization room accesses the website via account password and is responsible for randomization. Block randomization stratified by sex will be implemented and it is blind to those who enroll participants or assign interventions. In the immediate phase, the patients will receive an IMR test again after 30 min of intravenous infusion and the research nurses will record the IMR value. In the in-hospital follow-up period, complete blood count (CBC), serum electrolytes (potassium (K), sodium (Na), chloride (Cl)), liver function (alanine aminotransferase (ALT), aspartate aminotransferase (AST), bilirubin (BIL)), renal function (serum creatinine (Scr), blood urea nitrogen (BUN), uric acid (UA)), fasting glucose, lipid profile, cardiac troponin T/I (cTnT/cTnI), echocardiography, Seattle angina scale, quality of life scale, Holter electrocardiography, and 6-min walk test will be collected after continuous intravenous salvianolate 200 mg/day for 7 days.

All serious adverse events must be reported to the sponsor immediately or within 24 h in CRFs. The attending physicians are responsible for data entry. The data monitoring committee is responsible for data security and accuracy. Committee members ([name], [name], [name], and [name]) have access to the final dataset and periodically range check for data values.

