### Exclusion criteria during the follow-up periods

Patients who should not be enrolled but have been enrolled should be excluded. Patients who have received at least one dose of salvianolate or matching placebo but fail to complete the trial because of poor compliance or voluntary withdrawal should not be removed. Every withdrawal will be recorded in the case report forms (CRFs), and a visit will be arranged if possible. Although their data cannot be used for efficacy analysis, they can be used for safety analysis. The trial could be terminated in advance by investigators if there are any safety problems. Once it is terminated, all CRFs should be kept for future reference.

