### End points

The primary end point will be the IMR change in the immediate phase during the coronary angiography procedure, and the secondary end points will be the total ischemic burden assessed by the Seattle angina scale, quality of life scale, Holter electrocardiography, and 6-min walk test after 7 days before discharge. The safety end point will be the abnormal blood tests and self-reported adverse events.

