### Analysis

All data will be presented as percentages, mean ± standard deviation (SD), or median (quartile range). As the population variance *σ*^2^ is unknown, the confidence interval of the population mean *μ* is calculated by the formula $$ \overline{X}\pm \frac{S}{\sqrt{n}}{t}_{\alpha}\left(n-1\right) $$. Symbol $$ \overline{X} $$, *s*, and *n* are the sample mean, SD, and sample size, respectively, while *α* represents the significant level. The confidence interval of the difference between means will also be calculated by $$ \overline{X}\pm {S}_{{\overline{X}}_1-{\overline{X}}_2}{t}_{\raisebox{1ex}{$\alpha $}\!\left/ \!\raisebox{-1ex}{$2$}\right.}\left({n}_1+{n}_2-2\right) $$, in which $$ {S}_{{\overline{X}}_1-{\overline{X}}_2} $$ is the standard error of the difference of means. The adjusted Wald confidence intervals are used to estimate confidence intervals for proportions and the difference between the two population proportions [17].

IMR changes between the two groups will be compared by independent *t*-test or Mann-Whitney *U* test, while IMR changes before and after the use of salvianolate in the same group will be compared by paired *t*-test or Wilcoxon test. Analysis of covariance will be used if the baseline and follow-up IMRs are not highly correlated (*r* ≤ 0.8) [18, 19]. If the variables are not normally distributed, they will be transformed into normal distribution by logarithm. Different hypothesis testing, including *t*-test or nonparametric tests for continuous variables as well as *χ*^2^ test for categorical variables, will be used for the secondary end points assessed by the Seattle angina scale, quality of life scale, Holter electrocardiography, and 6-min walk test. The safety end point in our trial will be the abnormal blood tests including the abnormal liver function and self-reported adverse events such as dizziness and headache. The rate of abnormal liver function and other adverse events between the salvianolate group and the placebo group will be compared by *χ*^2^ test.

In our trial, stable CHD patients with myocardial microcirculatory disturbances form the population of interest, and participants with 50 to 70% stenosis in major coronary arteries, FFR > 0.80, and IMR > 25 form a sample. The end point of interest will be the IMR change in the immediate phase and the total ischemic burden assessed by the Seattle angina scale, quality of life scale, Holter electrocardiography, and 6-min walk test in the follow-up period.

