Premature discontinuation of salvianolate, loss to follow-up, and death are possible intercurrent events. As we use treatment policy strategy in our study, we will take a per-protocol analysis, as well as intention-to-treat (ITT) analysis for statistical analysis. Per-protocol analysis includes participants who complete the assigned therapy according to the trial protocol while ITT analysis includes all randomly assigned participants according to the treatment group to which they were originally assigned, regardless of the occurrence of intercurrent events. The ITT analysis will indicate how salvianolate will work in a more real-life setting. If there is evidence that the difference in the treatment depends on certain patient characteristics identified in the baseline assessment, a subgroup analysis will be performed.

The missing data before the intercurrent events will be filled with the measured values of “similar participants.” The similar patients should have the same sex and smoking history (smoker or nonsmoker). Missing values will be imputed by expectation-maximization algorithm through age, systolic blood pressure, diastolic blood pressure, fasting blood glucose, and IMR. Multiple imputation will be used in our study. *P*-value < 0.05 will be considered to indicate statistical significance. All statistical analyses will be performed using the Statistic Package for Social Science (SPSS) software package, version 18.0 (SPSS Inc., Chicago, IL, USA). The results will be published by the chief investigator and major contributors.

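### The safety data may miss dosed patients who stop early or are later found ineligible: the exclusion rule does not keep dosed ineligible patients, and the only scheduled follow-up bloods are placed after the full 7-day course

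*Protocol article*

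**What the plan says.** All references are to the protocol article.

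- **End points:** "The safety end point will be the abnormal blood tests and self-reported adverse events".
- **Analysis:** "The rate of abnormal liver function and other adverse events between the salvianolate group and the placebo group will be compared by" a chi-square test.
- **Table 2:** blood count, renal, electrolyte, liver and troponin tests are marked at screening (Day 1) and at in-hospital follow-up (Day 7), with nothing between. The table attaches no condition to Day 7.
- **Implementation and study procedures, text below Table 2:** the follow-up tests "will be collected after continuous intravenous salvianolate 200 mg/day for 7 days".
- **Exclusion criteria during the follow-up periods:** patients enrolled in error are to be excluded, with no exception for those already treated. Dosed patients who "fail to complete the trial because of poor compliance or voluntary withdrawal should not be removed". The section continues: "Every withdrawal will be recorded in the case report forms (CRFs), and a visit will be arranged if possible". It then says: "Although their data cannot be used for efficacy analysis, they can be used for safety analysis".
- **Analysis:** "Premature discontinuation of salvianolate, loss to follow-up, and death are possible intercurrent events". The same section names a treatment policy strategy and defines ITT as every randomised patient in the assigned group, whatever intercurrent events occur.

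**The concern.** A laboratory safety rate is only as complete as the set of dosed patients who have a post-dose sample and whose data are kept. Three statements put that at risk.

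First, the exclusion rule for patients enrolled in error, read as written, takes a treated patient out of the safety data. Such a patient (for example, one whose entry liver or renal value proves to be outside the limits in Table 1) is of particular interest for safety.

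Second, the sentence that protects non-completers names two reasons for not completing. An adverse event that leads the physician to stop treatment is not one of them.

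Third, the one scheduled follow-up panel is described as coming after seven days of infusion. A patient who stops on, say, Day 3 does not meet that description and is promised only that "a visit will be arranged if possible".

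If the missed patients differ from the others in how often they have abnormal results, the between-group comparison of liver abnormality is distorted. With 39 patients per group, a few missing panels are enough to matter.

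**Working it through.** **Step 1. Who stays in the safety analysis?** Four kinds of dosed patient, set against the text:

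| Dosed patient | What the article says |
|---|---|
| Completes 7 days | Panel at Day 7; included |
| Stops for poor compliance or own wish | Not removed; usable for safety |
| Stopped by the physician for an adverse event | Not named; covered only if counted as a withdrawal |
| Later found ineligible | Excluded, with no safety exception |

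The safety allowance follows the sentences on non-completers and withdrawals, and its subject is those patients. It does not reach back to those enrolled in error. The fourth row also conflicts with the ITT definition under Analysis, which keeps every randomised patient. Table 2 puts eligibility, randomisation and first infusion all on Day 1, so an eligibility error could come to light after dosing.

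**Step 2. Who has a post-baseline liver value?** Table 2 says Day 7. The text below it says after the seven-day course. For a completer these agree. For a patient who stops early but stays in hospital, the table gives a panel and the text does not. The withdrawal visit has no stated content.

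**Step 3. Do the analysis rules fill the gap?** ITT with a treatment policy strategy keeps a patient in the denominator but does not create a liver result. The imputation text concerns data missing before the intercurrent event and lists age, blood pressure, fasting glucose and IMR. It names no liver variable.

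**Step 4. Possible size.** The article gives no expected liver-abnormality rate, so there is no plan figure to reproduce for this point. Two plan inputs are used, both from Sample size: 39 per group and a 10% loss rate. The number of true abnormalities is assumed.

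- Unmeasured per group: 0.10 × 39 = 3.9, about 4, leaving 39 − 4 = 35 with a Day 7 panel.
- Let *a* be the true abnormalities among 39 and *k* the number of those among the 4 unmeasured. True rate = *a*/39; observed rate = (*a* − *k*)/35.

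| *a* (assumed) | True rate | *k* = 0 | *k* = 1 | *k* = 2 | *k* = 4 |
|---|---|---|---|---|---|
| 2 | 5.1% | 2/35 = 5.7% | 1/35 = 2.9% | 0/35 = 0% | not possible |
| 4 | 10.3% | 4/35 = 11.4% | 3/35 = 8.6% | 2/35 = 5.7% | 0/35 = 0% |
| 6 | 15.4% | 6/35 = 17.1% | 5/35 = 14.3% | 4/35 = 11.4% | 2/35 = 5.7% |

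If none of the unmeasured patients is abnormal, the observed rate is slightly too high. In these scenarios, if one or more is abnormal, it is too low. The direction is therefore not fixed. All of this applies only if those 4 patients have no bloods at a withdrawal visit, and the 10% is a general loss allowance, not a forecast of stopping for reactions.

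**The case against.** The other side has a good deal of force.

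- A reader might infer that only patients who stop for the two named reasons are kept. The article does not say so. It contains no such restriction, the next sentence covers every withdrawal, and nothing removes a patient because treatment was stopped for an adverse event. Someone who stops because of intolerance may also count as a voluntary withdrawal.
- A reader might infer that the liver rate comes solely from patients who tolerated the full course. Table 2 does not require completion, the sentence below it may simply describe the usual sequence, and a withdrawal visit may include bloods.
- A reader might infer that the whole safety comparison depends on finishing treatment, or that it must be biased towards no difference. Self-reported adverse events, 24-hour reporting of serious events and the committee's check that adverse events are recorded do not depend on finishing. Nor does the article show that early stopping is linked to liver abnormality, so the sign of any bias is unknown.
- A reader might infer that no blood result can be known during dosing. The article shows only that none is scheduled; it forbids no clinically indicated test.
- A condensed article commonly leaves the content of a withdrawal visit and the formal safety set to the full protocol or analysis plan.

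The last argument disposes of the visit's content as a finding in its own right. It does not remove what the article itself states: an exclusion rule with no exception for dosed patients that conflicts with its ITT definition, a retention sentence that names two reasons and omits the one most relevant to safety, and two different descriptions of when the panel is taken.

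**Conclusion.** The point holds in limited form. The firmest part is the exclusion of patients enrolled in error: applied as written, it drops dosed patients from the safety data, and it conflicts with the ITT set of all randomised patients. The other two parts are ambiguities. A physician-initiated stop for an adverse event is not expressly covered, and the single scheduled post-baseline panel is tied to Day 7 in one place and to completing the course in another.

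As regards early stopping, the consequence is confined to the laboratory part of the safety end point. That part may miss dosed patients; the article does not establish that it will. Under the assumptions above (4 of 39 unmeasured, and no bloods at a withdrawal visit), an assumed true rate of 10.3% could be reported as anything from 0% to 11.4%. These figures show sensitivity and are not a forecast. The correction is worth making because the groups are small and the change is cheap.

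**What to change.** 1. In Exclusion criteria during the follow-up periods, state that the safety analysis includes every patient who received any study infusion, whatever the reason for stopping and whether or not the patient is later found ineligible. Reconcile the exclusion of patients enrolled in error with the ITT definition under Analysis.
2. In Table 2 and the text below it, reconcile the timing of the follow-up panel, and state that the already planned Day 7 safety panel is collected when study treatment stops early.

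The cost is a few sentences and a planned blood draw brought forward in a few inpatients, about 4 per group if early stopping matched the plan's 10% loss allowance. No new type of test is needed.

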### End points

The primary end point will be the IMR change in the immediate phase during the coronary angiography procedure, and the secondary end points will be the total ischemic burden assessed by the Seattle angina scale, quality of life scale, Holter electrocardiography, and 6-min walk test after 7 days before discharge. The safety end point will be the abnormal blood tests and self-reported adverse events.

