### Inclusion and exclusion criteria

Seventy-eight stable CHD patients with 50 to 70% stenosis in major coronary arteries, FFR > 0.80, and IMR > 25 at Sir Run Run Shaw Hospital of Zhejiang University will be enrolled in this trial. Detailed inclusion and exclusion criteria are shown in Table 1. The attending physician of the patient is responsible for inclusion and exclusion assessment.

**Table 1 Tab1:** Inclusion and exclusion criteria

Inclusion criteria	Exclusion criteria
• Angina pectoris • CAG showed 50 to 70% stenosis in major coronary arteries; FFR > 0.8, IMR > 25; • Patients received no salvianolate treatment previously.	• Patients with left main disease; • Patients with severe cardiac insufficiency (New York Heart Association grade III or higher), severe renal insufficiency (eGFR < 60 ml/min), liver dysfunction (ALT > 3 × URL), and asthma history; • Severe cerebrovascular disease; infection, hematopoietic dysfunction, tumor or mental illness; • Combined malignant arrhythmia or third degree atrioventricular block; • Currently taking other Chinese herbs for the treatment of angina; • Pregnant or breastfeeding women; • Currently participating in other clinical trials; • Allergic to known ingredients of salvianolate; and • The investigator considers it unsuitable for inclusion in other circumstances, or the patient or family members do not agree with the study’s treatment plan.

*CAG*, coronary angiography; *FFR*, fractional flow reserve; *IMR*, index of microcirculatory resistance; *eGFR*, estimated glomerulus filtration rate; *ALT*, alanine aminotransferase; *URL*, normal reference level

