Risk factors for CHD such as smoking, old age, hyperlipidemia, diabetes, and mental stimulation can damage small coronary endothelium cells and affect coronary microcirculation [26]. Endothelial and smooth muscle dysfunction, sympathetic nerve dysfunction, microvascular atherosclerosis, and inflammation are closely related to microcirculation disorders [27]. The treatment of coronary microcirculation disorders can only rely on drugs, but currently, there is no clear and effective treatment of drugs. Salviae miltiorrhizae is a traditional Chinese herb and its effective ingredient salvianolate can protect the cardiovascular system at cellular levels [12]. It can inhibit the production of reactive oxygen species and increase the antioxidant capacity of cardiomyocytes [28], as well as improve microvascular reflow by inhibiting oxidative stress and apoptosis [16]. Previous study has demonstrated that five salviae miltiorrhizae-based preparations, including salvianolate injection, were effective in the treatment of stable angina pectoris with clinical improvement rate of 72.4 to 91.6% and electrocardiography improvement rate of 54.5 to 71.6% [29]. However, the effect of salvianolate intravenous infusion on the myocardial IMR in patients with high FFR and myocardial microcirculatory disturbance remains unclear. Accordingly, we focus on this issue and further explore the improvement effect of salvianolate on angina symptoms and myocardial ischemia.

Nonetheless, there are still limitations in this study. First, this study is a single-center participation study. Second, salvianolate will be compared with placebo only in this study, and there are no other comparative groups for effective drugs for coronary microcirculatory disturbances, such as angiotensin-converting enzyme inhibitors. Other non-inferiority and superiority trials may be needed. Although the study could only be designed based on the aforementioned limitations, we can still evaluate the effect of intravenous salvianolate infusion on IMR in stable CHD patients with high FFR and myocardial microcirculatory disturbance and test the improvement of the clinical symptoms of CHD patients with stable microcirculatory disturbance.

In conclusion, this study will clarify the effect of salvianolate on coronary microcirculation and provide an effective treatment for patients with stable CHD with high FFR and myocardial microcirculatory disturbances.

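### The laboratory safety end point counts abnormal status without reference to screening, so abnormalities carried in from entry dilute the between-arm comparison

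*Protocol article*

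**What the plan says.** The End points section of the protocol article gives the definition: "The safety end point will be the abnormal blood tests and self-reported adverse events". The Analysis section restates it ("The safety end point in our trial will be the abnormal blood tests including the abnormal liver function") and names the comparison: "The rate of abnormal liver function and other adverse events between the salvianolate group and the placebo group will be compared", by a chi-square test. In both places a test counts for being abnormal. Neither mentions the patient's value before treatment.

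On liver tests, Table 1 excludes only "liver dysfunction (ALT > 3 × URL"). It sets no limit for AST or bilirubin, the other two liver tests in the panel.

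Table 2 schedules the whole blood panel at screening and again at Day 7. The text under Table 2 confirms that the second set "will be collected after continuous intravenous salvianolate 200 mg/day for 7 days". Table 2 also schedules vital signs in the immediate phase, around the first infusion.

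The Trial committees section makes the data monitoring committee responsible for ensuring that every adverse event is recorded. It does not limit this to events that the patient reports.

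**The concern.** A safety end point should measure what happened under treatment. Here the tested rate is one of status: a liver test abnormal at entry and unchanged on Day 7 looks the same as one that became abnormal on the drug. The entry criteria admit such patients. The primary end point in the same section is expressed as a change, so the contrast in wording is visible within the document.

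Carried-over abnormalities are unrelated to treatment and are expected equally in both arms. They raise both rates and so shrink the risk ratio and add noise. In an efficacy comparison that would be conservative. In a safety comparison it favours a finding of no difference.

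A second point concerns the word self-reported. A change seen in the scheduled immediate-phase vital signs, in a patient who mentions nothing, falls outside the end point as worded. Under the Trial committees section, an adverse event observed in that way should be recorded.

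**Working it through.** **Plan's own figure.** The protocol gives no rate, power or sample size for safety. The only number taken from it is 39 per arm (Sample size section). The stated equation with a one-sided α of 0.05, 80% power, σ = 20 and an effective difference of |20 − 40 + 8| = 12 gives n = 34.35, so 35. Then 35/0.9 = 38.9, so 39 per arm. The safety point does not depend on how that figure was reached.

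**Assumptions, none of them in the documents.**
- e = probability of a new abnormality among patients normal at entry: 20% on salvianolate, 2.5% on placebo.
- b = share of patients abnormal at entry and still abnormal on Day 7, equal in both arms: 0, 10%, 20%, 40%.
- All 39 per arm have a Day 7 result. Test: uncorrected chi-square, two-sided 5%. Power is the exact sum over the two binomial distributions.

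**Formulas.**
- As worded (every abnormal result counts): p = b + (1 − b)e.
- New abnormalities only: p = (1 − b)e.

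**Example at b = 20%.**
- As worded: placebo 0.20 + 0.80 × 0.025 = 0.22; salvianolate 0.20 + 0.80 × 0.20 = 0.36. Risk ratio 0.36/0.22 = 1.64.
- New only: placebo 0.80 × 0.025 = 0.02; salvianolate 0.80 × 0.20 = 0.16. Risk ratio 8.0.
- The absolute difference is 0.14 both ways. Its standard error as worded is √[(0.22 × 0.78 + 0.36 × 0.64)/39] = 0.102. For new only it is √[(0.02 × 0.98 + 0.16 × 0.84)/39] = 0.063. The same signal is measured against more noise.

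**Results.**

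| b | Rates as worded (placebo, salvianolate) | Risk ratio as worded | Power as worded | Rates, new only | Power, new only |
|---|---|---|---|---|---|
| 0 | 2.5%, 20% | 8.0 | 78% | 2.5%, 20% | 78% |
| 10% | 12.25%, 28% | 2.29 | 42% | 2.25%, 18% | 73% |
| 20% | 22%, 36% | 1.64 | 28% | 2%, 16% | 67% |
| 40% | 41.5%, 52% | 1.25 | 16% | 1.5%, 12% | 51% |

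The right comparison is across a row. The 78% in the first row applies only if nobody is abnormal at entry, and no redefinition recovers it, because a patient already abnormal cannot become newly abnormal. Across rows the gain is about 31, 38 and 35 percentage points at b = 10%, 20% and 40%.

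**Sensitivity to the assumed effect, at b = 20%.** With new abnormalities in 25% v 5%, power is 34% as worded and 65% new only. With 15% v 2%, it is 18% and 49%. The direction does not change.

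**Adverse events.** The End points and Analysis sections restrict the end point to self-reported events, while the Trial committees section requires all adverse events to be recorded. An event noticed by staff during the infusion is therefore recorded under one section and left out of the end point under the other two.

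**The case against.** The strongest reply is that the article leaves the word abnormal undefined. Thresholds and treatment-emergent rules often sit in the full protocol or the analysis plan, and drawing the same tests at screening and Day 7 fits a change-based reading. This is fair as far as thresholds go, and their absence is not criticised here. It does not fully answer the point. The article states the end point twice and names the rate to be tested, each time in terms of status. Followed as written, it gives the diluted comparison.

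A reader might infer three stronger claims that the documents do not support.

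- *That every abnormal Day 7 result enters one pooled count, with glucose and lipids making most patients abnormal before treatment.* Those tests are in the panel and fall literally under abnormal blood tests. But the named comparison covers liver function and other adverse events, and no pooled count is described.
- *That drug harm is hidden.* Randomisation balances carried-over abnormalities in expectation. They dilute the contrast and lower power without erasing it. The ALT limit shows that raised ALT may enter, not that it is common.
- *That haemodynamic events during the infusion go unrecorded.* The Trial committees section requires all adverse events to be recorded. What remains is a conflict over whether observed events reach the end point.

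It is also true that the trial is sized for IMR and that safety in 78 patients is secondary. That limits the weight of the point, but the remedy costs very little.

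**Conclusion.** The concern holds in a limited form. The laboratory safety end point is worded by status, the entry criteria admit patients with raised ALT, and the screening values that would separate old from new abnormalities are collected but not used in the definition. The result is dilution towards no difference.

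The size is illustrative: it rests on assumed event rates, on carry-over being equal in both arms, and on complete Day 7 data. If few patients are abnormal at entry, the loss is small; at 10% carry-over it is already about 31 points of power under the main assumption. Counting worsening as well as new abnormality could recover somewhat more than the new-only figures, but this was not modelled.

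The adverse-event wording is an inconsistency to reconcile, not evidence that events will be missed.

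**What to change.** In the End points and Analysis sections, count a laboratory abnormality as a safety event only if it is new or worsened relative to the patient's screening value. Apply the chi-square comparison of liver function to that rate, and report screening-to-Day 7 shift tables for the blood tests.

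In the same two sections, reconcile the self-reported wording with the Trial committees section, so that observed adverse events also enter the safety comparison. These include events seen in the immediate-phase vital signs that Table 2 already schedules.

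The cost is a change of wording and one set of tables, with no added visit, blood draw or patient. There are two small downsides. Patients abnormal at entry contribute an event only if they worsen, and the trial team must set a worsening rule for each test, preferably before any unblinded data are seen.

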### Trial committees

[name] guides the research team and provides overall supervision for the trial. The data monitoring committee ([name], [name], [name], and [name]) is responsible for reviewing and monitoring data safety. They need to make sure that all CRFs are filled out correctly and consistent with the original data and that all adverse events have been recorded and all serious adverse events have been reported in accordance with the relevant procedures. Investigators have the right to reveal a participant’s allocated intervention or terminate the study in advance after discussion with [name] in the event of safety issues during the study as well as notify the ethics committee.

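### The safety end point counts only self-reported adverse events, which does not match the duty to record all adverse events or the planned between-group comparison

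*Protocol article*

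**What the plan says.** The protocol article defines the safety end point twice. Under End points: "The safety end point will be the abnormal blood tests and self-reported adverse events". Under Analysis, with examples: "abnormal blood tests including the abnormal liver function and self-reported adverse events such as dizziness and headache". Both definitions limit the non-laboratory part to what patients report themselves.

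Three other statements carry no such limit:

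- Analysis, in the sentence right after the second definition, sets the test: "The rate of abnormal liver function and other adverse events between the salvianolate group and the placebo group will be compared by" a chi-square test.
- Trial committees asks the data monitoring committee to make sure that "all adverse events have been recorded and all serious adverse events have been reported in accordance with the relevant procedures".
- Implementation and study procedures adds: "All serious adverse events must be reported to the sponsor immediately or within 24 h in CRFs".

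Death is named once as an event that may occur to a participant in the trial, among the intercurrent events in the Analysis section: "loss to follow-up, and death are possible intercurrent events". No section places it in the safety end point.

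**The concern.** A safety end point should cover the harms that a trial is obliged to collect, whoever notices them first. Here the definition is narrower than the collection. A death cannot be self-reported. The first infusion runs during coronary angiography, where staff may well see a reaction before the patient mentions it. Under the literal definition such events are recorded on the case report form and reported to the sponsor, but they do not belong to the end point.

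What is at stake is which events count in the only between-group comparison of harms that the article states. If the wording stays open, the choice between self-reported and all recorded events can be made after the data are seen. Two analysts following the same text could then report different safety results.

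**Working it through.** The documents give no figure on this point, so there is nothing to reproduce. The check sets the statements side by side.

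| Statement | Section | Which adverse events |
|---|---|---|
| First definition of the safety end point | End points | Self-reported only |
| Second definition | Analysis | Self-reported only; examples are dizziness and headache |
| Between-group test | Analysis | Other adverse events, no limit stated |
| Recording duty | Trial committees | All |
| Serious event reporting | Implementation and study procedures | All serious events |

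**Step 1: definition against collection.** The first two rows are narrower than the last two. The difference consists of events not reported by the patient: death, and anything that only staff detect. The laboratory part of the end point closes some of this gap. Table 2 schedules blood count, renal and liver function, electrolytes and troponin at Day 7, and abnormal results count however they come to light. Blood tests do not, however, capture a death or an observed reaction as such.

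**Step 2: definition against test.** The comparison sentence can be read in two ways.

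- *Narrow reading.* The sentence follows directly on the self-reported definition and mirrors its two parts, first liver function and then adverse events. On this reading, other adverse events means the self-reported ones just named. Death and staff-detected events are then outside both the end point and the test.
- *Broad reading.* The words are taken as they stand, and the test covers all recorded adverse events. Death and staff-detected events are then compared, but the tested outcome is wider than the end point defined twice.

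**Step 3: does either reading make the text consistent?** No. The narrow reading agrees with the definitions but drops events that the trial must record. The broad reading agrees with the recording duty but contradicts both definitions. The passages need to be reconciled whichever was intended.

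**The case against.** The strongest reply is that this is loose wording and nothing more. Self-reported may be shorthand for clinical events as opposed to laboratory ones. The sentence that sets the test omits the qualifier. All adverse events must be recorded, serious ones go to the sponsor within 24 h, and dosed patients who withdraw stay available for the safety analysis (Exclusion criteria during the follow-up periods). Nothing in the article suggests that serious events or deaths would go unreported by group.

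Much of this stands, and it limits the finding. A reader might go further and infer any of the following:

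- **Deaths, arrhythmias and staff-observed reactions are excluded from the comparison of salvianolate with placebo.** The article does not say so. The comparison sentence admits the broad reading.
- **Mild symptoms will drive the safety result.** This is unsupported, because the laboratory half of the end point is found by staff and includes troponin.
- **Electrocardiography and echocardiography are wrongly left without a safety analysis.** How such data are tabulated is commonly left to a full protocol or analysis plan, neither of which is shown.
- **The restriction costs a stated amount of power.** The documents give no adverse event rates and no share of events that patients report. A power figure would rest on invented rates, and rates high enough to show a marked loss would not fit rare serious harms. With 39 patients per group, a chi-square test says little about such harms under either definition.

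The reply does not remove the inconsistency itself. The restrictive wording is stated, and stated twice, so it is not a detail left to another document.

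**Conclusion.** Wrong as written, as an internal inconsistency of minor to moderate severity. The twice-stated self-reported definition matches neither the duty to record and report all events nor the unrestricted wording of the comparison.

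The effect on the trial's safety conclusion cannot be quantified from the documents. One consequence needs no assumed rate: taken literally, a death itself contributes nothing to the safety end point in either group. Whether deaths and staff-detected events would also be missing from the comparison depends on which reading the sponsor intended, and the article does not settle that. The conclusion rests only on the article's wording. A full protocol or analysis plan with a single wider definition would resolve the matter in practice, but the published text would still need correcting.

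**What to change.** In End points and in Analysis, define the safety end point as abnormal blood tests plus all adverse events and serious adverse events recorded in the case report form, including death, whether reported by the patient or found by staff.

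Use the same definition in the comparison sentence. Give the number of patients with any adverse event and with any serious adverse event in each group, with the adjusted Wald interval that the Analysis section already plans for proportions and their difference. Self-reported symptoms such as dizziness and headache may stay as a descriptive subset.

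This changes how an outcome is defined and counted and touches no treatment rule. The cost is rewording in two sections and a few more table rows. The events must already be recorded, so no visit, test or staff is added. Under the article's Amendments section, a revision after the start of the study needs ethics committee approval before it is implemented.
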